3.2. Giemsa stain

- Place the slides in a staining rod/rack
- Do not fix the films before staining.
- Cover the air-dried smear with a 1:10 diluted Giemsa using buffered distilled water at pH 7.2 (recommended for malaria parasites in order to stain schuffner’s granules) as a diluents
  - 1:10 Giemsa =1 part of stock Giemsa + 9 parts buffered water
- stain the slides as follows:
  - 30 min if using 3% stain solution
  - 10 min if using 10% stain solution
- Wash the stain from the slide gently using clean water (not necessarily distilled water or buffered water)

Wipe the back of each slide clean and place it in draining rack for the preparation to air dry

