**Inclusion and exclusion criteria**

Patients will be selected on the basis of the following WHO criteria:

- Patients 6 months and above
- Absence of severe malnutrition characterized by standard of WHO protocol
- A slide-confirmed infection with *P.vivax* only (i.e. no mixed infections).
- Initial parasite densities greater than 250 asexual parasites/μl
- Patients with no other signs of severe and complicated malaria according to current WHO definitions
- Having the measured axillary temperature 37.5 °C
- Ability to attend the stipulated follow-up visits, and easy access to the health facility.
- Informed consent provided by patient or parent/guardian
- ability to swallow oral medication;
- absence of concomitant febrile diseases
- absences of history of allergic reaction to CQ treatment
- ability and willingness to comply with the protocol for the duration of the study and to comply with the study visit schedule;

Individuals who did not fulfill the above criteria and the followings will not include:

- Study subjects who are Pregnant or lactating or
- The existences of underlying chronic severe illness (e.g. cardiac, renal, hepatic diseases, HIV/AIDS) will not consider as study subjects.

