# Budget break down

Chemicals and reagents

| Serial no | Items | Unit | Quantity | Unit Price | | Total Price | | |
| --- | --- | --- | --- | --- | --- | --- | --- | --- |
| Birr | Cents | Birr | | Cents |
|  | Microscopic slide | Pack | 20 | 49 | 00 | 980 | 00 | |
|  | RDT | Kits | 550 | 15 | 00 | 8250 | 00 | |
|  | Cotton | pack | 5 | 14 | 75 | 82 | 35 | |
|  | 70% Alcohol | Liter | 5 | 18 | 20 | 91 | 00 | |
|  | Syringes | Pack | 450 | 10 | 00 | 4500 | 00 | |
|  | EDTA Test tube | Pack | 100 | 25 | 00 | 2500 | 00 | |
|  | Lancet | Pack | 3 | 40 | 35 | 121 | 15 | |
|  | Giemsa stains | Liter | 15 | 20 | 00 | 300 | 00 | |
|  | Methyl alcohol | Liter | 2 | 90 | 85 | 181 | 70 | |
|  | Distilled water | Liter | 20 | 10 | 25 | 205 | 00 | |
|  | Oil immersion | Bottle | 3 | 10 | 45 | 31 | 15 | |
|  | 5% Bleach | Liter | 5 | 100 | 00 | 500 | 00 | |
|  | Washing soap | Pcs | 10 | 10 | 00 | 100 | 00 | |
|  | Slide box | Pieces | 4 | 45 | 75 | 182 | 15 | |
|  | Digital camera | Pieces | 1 | 2000 | 00 | 2000 | 00 | |
|  | Examination Glove | Pack | 5 | 30 | 00 | 150 | 00 | |
|  | Heavy duty glove | Pcs | 5 | 20 | 00 | 100 | 00 | |
|  | Capillary tubes | Pack | 5 | 100 | 00 | 500 | 00 | |
|  | Sealant | Pack | 3 | 50 | 00 | 150 | 00 | |
| **Sub total** | | | | | | **20, 923** | **00** | |

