**Annex-1 Laboratory procedures**

**3.1.** Method of sample collection capillary blood collection

1. Rub the site vigorously with cotton or a gauze pad moistened with 70% alcohol
2. After the skin has dried, make a puncture 2-3mm deep with a sterile lancet. A rapid and firm puncture should be made with control of the depth
3. a freely flowing blood should be taken and will make thick and thin blood films.
4. Stop the blood flow by applying slight pressure at the site preferably with a gauze pad

Preparation of thick blood film

- Place a small drop of blood on a clean slide
- spread it with an applicator stick or the corner of another slide until small prints are just visible through the blood smear
- The prepared smear corresponds to a circle of approximately 2cm diameter.

Preparation Thin blood film

1. Place a small drop of well mixed EDTA blood (about 2-3 mm) or freshly collected from capillary blood sites , 1.0 cm from the end of the glass slide, using either a plain capillary tube or other type of blood dropping device

- when the blood is from an anemic patient larger drop of blood should be used
- If capillary blood to be used, the procedure will follow SOP for proper collection of capillary blood

1. the spreading slide is placed in front of the drop of blood at an angle of about 30o - 40 o to the slide and then is moved back to make contact with the drop (both the spreader and the base slide should be free from grease)
2. The drop will spread out quickly along the line of contact of the spreader with the slide
3. As the drop of blood spreads, be careful not to let it spread to both edges of the spreader
4. The spreader is advanced with a smooth steady motion so that a thin film of blood is spread over the slide
5. Allow the smear to air-dry

- Also do not use heat for drying

1. Label the name of the patient and date or reference number is written on the head of the film using a lead pencil, a diamond marker or a graphite

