**Microscopic blood examination**

Thick and thin blood films for parasite counts will be obtained and exam­ined at screening on day 0 to confirm adherence to the inclusion and exclu­sion criteria. Thick blood films will be also examined on days 2, 3, 7, 14, 21and 28, or any other day if the patient returns spontaneously and parasitological reassessment is required. Specimens will be labelled anony­mously (screening number or study number, day of follow-up, date).

A fresh Giemsa stain dilution (10%v/v) will be prepared at least once a day and possibly more often, depending on the number of slides to be processed. Giemsa-stained thick and thin blood films will be examined at a magnifica­tion of 1000× to identify the parasite species and to determine the parasite density.

Two blood slides per patient will be obtained: one thick blood smear and one thin blood smear. Thick blood slide will be stained by 10% Giemsa for 10–15 min for initial screening. Moreover, if the patients are subsequently enrolled, the same staining will be used for all slides obtained at follow-up visits. The study number of the patient, the date and the day of follow-up will be recorded either on the frosted edge of the slide or on the glass with a permanent glass pen.

The thick blood smear for initial screening will be used to count the numbers of asexual parasites and white blood cells in a limited number of microscopic fields.

Thin blood smear will be used to calculate the parasite density, by counting the number of asexual parasites in a set number of white blood cells (typically 200), using the following formula:

Parasite density (per µl) =
[figure not shown]

[figure not shown]

The same technique will be used to establish the parasite count on each subsequent blood film. When the number of asexual parasites is less than 10 per 200 white blood cells in follow-up smears, counting will be done against at least 500 white blood cells (i.e. to completion of the field in which the 500th white blood cell is counted). A blood slide will be considered negative when examination of 1000 white blood cells reveals no asexual parasites. The presence of gametocytes on an enrolment or follow-up slide will be noted, but this information will not contribute to basic evaluation.

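### The Giemsa procedure bars fixing any film, thin films included, which weakens the Day 0 thin-film check of P. vivax mono-infection and the thin-film density count

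*Protocol*

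**What the plan says.** Annex-1 of the protocol describes how to make a thick film and then a thin film. The thin-film steps finish with drying ("Allow the smear to air-dry") and labelling, with no fixation step. Section 3.2, Giemsa stain, follows directly and gives one procedure for both: "Do not fix the films before staining". It then has the smear covered with Giemsa diluted one part in ten with buffered water at pH 7.2, a value "recommended for malaria parasites in order to stain" Schüffner's granules.

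The section Microscopic blood examination states "Two blood slides per patient will be obtained: one thick blood smear and one thin blood smear". It uses both kinds of film on Day 0 to check eligibility: "Giemsa-stained thick and thin blood films will be examined" to identify the species and the density. It also assigns the density calculation to the thin smear.

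The inclusion criteria require a slide-confirmed infection with P. vivax "only (i.e. no mixed infections"). They do not say which film confirms it. The budget lists 2 litres of "Methyl alcohol" as a separate line from the 70% alcohol, and no procedure says what it is for.

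**The concern.** A thick film is stained unfixed on purpose: the red cells burst and a larger volume of blood can be searched. A thin film serves the opposite purpose, since it keeps the red cells intact so that their size, shape and stippling help to separate one species from another. An instruction that leaves both kinds unfixed suits the first and defeats the second.

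Mono-infection with P. vivax defines the study population. If a mixed infection is missed on Day 0, the patient is enrolled and treated as a vivax case. The definitions of early and late failure refer to parasitaemia without naming a species, so parasites seen later may be counted against chloroquine. The study has one arm, so no comparator would offset such an error.

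Density is also involved. The Day 0 count decides whether the patient passes the threshold of 250 asexual parasites per microlitre, and it is the reference for the Day 2 and Day 3 early-failure criteria.

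**Working it through.** No arithmetic reproduces or tests this point, because it turns on a laboratory instruction. The check is to set the relevant sections side by side.

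1. **Does the ban reach thin films?** Section 3.2 speaks of films in the plural and comes straight after both preparations. It tells staff to cover an air-dried smear, and in Annex-1 air-drying appears only among the thin-film steps. It chooses its pH to show Schüffner's granules, which lie in the infected red cell and are seen best when that cell is preserved. Read as written, thin films are included.

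2. **Does another section correct it?** Microscopic blood examination has some staining text of its own: 10% Giemsa for 10–15 minutes for the thick slide at screening, and the same staining for slides at follow-up visits. It neither mentions fixation nor gives a thin-film step. Quality control covers checking the stain against known positive samples, not fixation. Nothing overrides section 3.2.

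3. **What happens to an unfixed thin film?** The stain is nine parts buffered water to one part stock, and unfixed red cells lyse in it. This premise comes from general laboratory knowledge; the protocol does not state it.

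4. **What does the plan ask of the thin film?** Two things: a share in species identification on Day 0, together with the thick film ("Giemsa-stained thick and thin blood films will be examined at a" set magnification for that purpose), and the density calculation. The first loses most of its value without intact red cells. The second would be made on a degraded film. Because the count is taken against white cells, neither the direction nor the size of any error in density can be stated.

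5. **What remains?** The thick film is a separate slide, is correctly left unfixed, and is also read for species. After Day 0 the schedule in Microscopic blood examination names thick films only.

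6. **Do the safeguards repair the thin film?** Every slide is read by two microscopists, a third reader settles discordant species calls, and all Day 0 slides are cross-checked by a senior technician from the regional laboratory. These steps reduce reader error on both slides. They cannot restore lysed cells on the thin slide, and if both readers miss the same second species there is no discordance to call in the third.

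**The case against.** The best reply is that section 3.2 is a thick-film procedure that has lost its label. Its 10 minutes in 10% stain agrees with the thick-slide staining given under Microscopic blood examination, and the budgeted methyl alcohol suggests that someone expected to fix thin films. Experienced technicians may well do so unprompted. This is plausible, but the protocol does not say it, and a technician who fixes the thin film departs from the written procedure.

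Other parts of the reply stand and limit the point:

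- A reader might infer that the mono-infection criterion cannot be applied reliably, or that the thin film is the test that confirms it. The protocol supports neither. The criterion asks only for slide confirmation, and species is read on both films.
- A reader might infer that species calls at follow-up are unreliable too. The follow-up schedule names only thick films, for which no fixation is correct.
- A reader might infer that every missed mixed infection ends as a chloroquine failure. Under Protocol violation and withdrawn, a patient found during follow-up to carry another species alone is withdrawn and so not counted as a failure.
- The double reading and the Day 0 cross-check remain fully useful on the thick slide.
- The budget also holds 550 RDT kits. Their type and role are not stated, so they neither rescue the species check nor can be ruled out as a help.

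**Conclusion.** The point holds as a flaw in a laboratory procedure. The written staining steps bar fixation of the thin film, and following them would cost most of the thin-film contribution to confirming P. vivax mono-infection on Day 0 and degrade the smear used for density. The conclusion rests on the plain reading of section 3.2 and on the outside premise that unfixed red cells lyse in diluted stain. The criterion is weakened because one of its two films is impaired; it is not made unusable. No endpoint definition, sample size or analysis changes.

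The size cannot be derived from the protocol. A reader might assume that 2% to 5% of the 422 patients (422 × 0.02 = 8.4; 422 × 0.05 = 21.1) carry an unrecognised mixed infection, and take the 5.76% failure rate quoted in the Introduction as the base:

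- If all of them show parasitaemia again and count as failures: 0.98 × 5.76% + 2% = 7.6%, and 0.95 × 5.76% + 5% = 10.5%.
- If none do: 0.98 × 5.76% = 5.6%, and 0.95 × 5.76% = 5.5%.

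These figures show how sensitive the failure rate is to an assumed share of mixed infections. They do not measure the effect of leaving thin films unfixed: some mixed infections would be missed on a well-fixed film as well, the thick film would catch others, and the withdrawal rule would remove some from the failures.

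**What to change.** In section 3.2, replace the single instruction with separate steps for each film: fix thin films with methyl alcohol and let them dry before staining; do not fix thick films. Bring the thin-film preparation steps in Annex-1 and the staining text under Microscopic blood examination into line, so that all three places agree on how each film is handled.

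The inclusion criteria can stay as they are. Requiring confirmation on the fixed thin film alone would add a single-film rule where the plan uses both films.

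The cost is a sentence or two in the annex and a short extra step per thin slide. The reagent is already listed (2 litres at 90.85 birr, 181.70 birr in total). The change should be made before enrolment, because a thin film stained unfixed cannot be recovered.

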3.3. Heamatocrite procedure

- If capillary blood from finger puncture is to be used, follow SOP for capillary blood collection
- If anticoagulated venous blood, mix specimen well
- Allow the blood to enter the tube by capillarity
- Fill 3/4th of the capillary tube ; do in duplicate
- Seal the capillary tubes by vertically placing the dry end into a tray of sealing compound (wax or plasticin)
- Rotate the capillary tube slightly and remove it from the tray. The sealant plug should be 4-6mm long. Inspect the seal for a flat bottom.

Place the filled, sealed capillary tube in the groove (slots) of the centrifuge with the sealed end toward the periphery.

- Set the timer of the centrifuge at 5 minute and spin at 10,000-15,000g.
- Read the PCV using a reading device that is either part of the centrifuge or separate from it

**Microscopic blood examination**

Thick and thin blood films for parasite counts will be obtained and exam­ined at screening on day 0 to confirm adherence to the inclusion and exclu­sion criteria. Thick blood films will be also examined on days 2, 3, 7, 14, 21and 28, or any other day if the patient returns spontaneously and parasitological reassessment is required. Specimens will be labelled anony­mously (screening number or study number, day of follow-up, date).

A fresh Giemsa stain dilution (10%v/v) will be prepared at least once a day and possibly more often, depending on the number of slides to be processed. Giemsa-stained thick and thin blood films will be examined at a magnifica­tion of 1000× to identify the parasite species and to determine the parasite density.

Two blood slides per patient will be obtained: one thick blood smear and one thin blood smear. Thick blood slide will be stained by 10% Giemsa for 10–15 min for initial screening. Moreover, if the patients are subsequently enrolled, the same staining will be used for all slides obtained at follow-up visits. The study number of the patient, the date and the day of follow-up will be recorded either on the frosted edge of the slide or on the glass with a permanent glass pen.

The thick blood smear for initial screening will be used to count the numbers of asexual parasites and white blood cells in a limited number of microscopic fields.

Thin blood smear will be used to calculate the parasite density, by counting the number of asexual parasites in a set number of white blood cells (typically 200), using the following formula:

Parasite density (per µl) =
[figure not shown]

[figure not shown]

The same technique will be used to establish the parasite count on each subsequent blood film. When the number of asexual parasites is less than 10 per 200 white blood cells in follow-up smears, counting will be done against at least 500 white blood cells (i.e. to completion of the field in which the 500th white blood cell is counted). A blood slide will be considered negative when examination of 1000 white blood cells reveals no asexual parasites. The presence of gametocytes on an enrolment or follow-up slide will be noted, but this information will not contribute to basic evaluation.

Two qualified microscopists will read all the slides independently, and para­site densities will be calculated by averaging the two counts. Blood smears with discordant results (differences between the two microscopists in species diagnosis, in parasite density of > 50% or in the presence of parasites) will be re-examined by a third, independent microscopist, and parasite density will be calculated by averaging the two closest counts.

Annex-: Dosing chart of CQ

Tablets of Chloroquine 150mg base or syrup 50mg base per 5ml(note: one 250mg chloroquine phosphate salt tablet contains 150mg chloroquine base). Total dose of 25 mg base per kg over 3 days(10mg base per kg on day 1, 10 mg base per kg on day 2 and 5 mg base per kg on day 3).

| **Weight(Kg)** | **Age** | **Dosage** | | |
| --- | --- | --- | --- | --- |
| **Day 1** | **Day 2** | **Day 3** |
| 7-10 | 4-11 months | ½ tablet | ½ tablet | ½ tablet |
| 11-14 | 1-2 years | 1 tablet | 0.5 tablet | 0.5 tablet |
| 15-18 | 3-4 years | 1 tablet | 1 tablet | 1tablet |
| 19-24 | 5-7 years | 1 ½ tab | 1 ½ tab | 1 tab |
| 25-35 | 8-11 | 2 ½ tab | 2 tab | 1 tab |
| 36-50 | 12-14 | 3 tab | 2tab | 2 tab |
| 51 and above | 15 yrs and above | 4 tab | 4 tab | 2 tablets |

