The emergence of resistance to anti malarials threatens efforts towards malaria control and elimination. Resistance to Drugs has been implicated in the spread of malaria to new areas and re-emergence of malaria in areas where the disease had been eliminated. It also plays significant role in the occurrence and severity of epidemics in some parts of the world [15] and results in an ongoing diseases transmission. Therefore, there is a need to monitor, the status of drug resistance to anti-malarials on continuous and regular basis (often at 2 years interval. To do so, three main tools are used for drug resistance monitoring and assessing which includes therapeutic efficacy tests (*In* vivo*)*, in vitro tests, and analyses of molecular markers.

Therapeutic efficacy assessment according to the standard protocol of the WHO is the most useful for updating national treatment policies. These include, therapeutic assessment based on evaluation of the clinical and parasitological outcomes remains the mainstay of monitoring the efficacies of anti-malarial regimens and is recommended [16]. Measures such as parasite clearance time, fever clearance time or gametocyte clearance time in vivo and in vitro assays are used to indirectly detect any variation in parasite sensitivity thereby facilitating early warning in case of emergence of tolerance or resistance [17, 18].

In Ethiopia, Chloroquine 150 mg base tablet *OR* chloroquine syrup 50 mg base is the first line drug of choice for the treatment of vivax malaria. The ideal dose is 10 mg base/kg po immediately (Day 1), followed by 10 mg base/kg po at 24 hours (Day 2), and 5mg base/kg po at 48 hours (Day 3) for a total dose of 25 mg chloroquine base/kg over three days with a maximum total of 1,500 mg chloroquine base (maximum of 2,500 mg chloroquine phosphate salt) over three days in three divided doses [19].

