**Independent variables**

- **Socio-demographic variables:** Questionnaire will be developed which can assess sex, age, and educational status with socio-economic status of the population.
- **Body weight:** Body weight will be recorded on day 0 to the nearest kilogram on a Salter scale or on a hanging scale for young children.

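### In the chloroquine dosing chart, the 11-14 kg and 36-50 kg rows give a second-day dose below the stated 10 mg base/kg at every weight in the band

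*Protocol*

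**What the plan says.** The dosing annex lists "Tablets of Chloroquine 150mg base or syrup 50mg base per 5ml" and states the regimen in words: 25 mg base/kg in total, as 10 mg/kg on day 1, "10 mg base per kg on day 2 and 5 mg base per kg on day 3". The Introduction gives the same regimen twice. Its account of Ethiopian practice adds the timing, with the first dose given at once, "followed by 10 mg base/kg po at 24 hours (Day 2)", and "5mg base/kg po at 48 hours (Day 3)", and a ceiling: "with a maximum total of 1,500 mg chloroquine base".

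The chart under that statement converts the regimen to tablets by weight band. The two rows at issue read "11-14 | 1-2 years | 1 tablet | 0.5 tablet | 0.5 tablet" and "36-50 | 12-14 | 3 tab | 2tab | 2 tab". In both, the second-day count equals the third-day count and is lower than the first-day count.

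**The concern.** The stated regimen has two equal doses followed by a half dose. These two rows have one larger dose followed by two equal smaller ones, so the second dose comes out low and the third high. The chart is the only place where the protocol turns mg/kg into tablet counts, so staff will in practice dispense from it. In a single-arm study of one fixed regimen, patients dosed from these rows would receive a different daily schedule from the one the protocol says it tests. The low dose falls at 24 hours, before the Day 2 parasite count used to define early treatment failure.

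**Working it through.** **Inputs.** Tablet strength 150 mg base, the tablet counts and the weight bands come from the dosing annex. Whole-kilogram weights are used because "Body weight will be recorded on day 0 to the nearest kilogram" (Independent variables).

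**Formula.** Dose in mg/kg = 150 × tablets ÷ weight.

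**Closed rows, lightest to heaviest weight (mg base/kg).**

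| Band (kg) | Tablets | Day 1 | Day 2 | Day 3 | Total |
| --- | --- | --- | --- | --- | --- |
| 7-10 | 0.5 / 0.5 / 0.5 | 10.7-7.5 | 10.7-7.5 | 10.7-7.5 | 32.1-22.5 |
| **11-14** | 1 / 0.5 / 0.5 | 13.6-10.7 | **6.8-5.4** | 6.8-5.4 | 27.3-21.4 |
| 15-18 | 1 / 1 / 1 | 10.0-8.3 | 10.0-8.3 | 10.0-8.3 | 30.0-25.0 |
| 19-24 | 1.5 / 1.5 / 1 | 11.8-9.4 | 11.8-9.4 | 7.9-6.3 | 31.6-25.0 |
| 25-35 | 2.5 / 2 / 1 | 15.0-10.7 | 12.0-8.6 | 6.0-4.3 | 33.0-23.6 |
| **36-50** | 3 / 2 / 2 | 12.5-9.0 | **8.3-6.0** | 8.3-6.0 | 29.2-21.0 |

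**Second-day dose in the two rows.**
- 11-14 kg: 75 ÷ 11 = 6.8 and 75 ÷ 14 = 5.4.
- 36-50 kg: 300 ÷ 36 = 8.3 and 300 ÷ 50 = 6.0.
- The shortfall against 10 runs from 1 − 8.33/10 = 17% to 1 − 5.36/10 = 46%.
- Every other closed row reaches 10 mg/kg at its light end.

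**Does tablet rounding explain the second-day dose?** Compare half-tablet choices by their worst gap from 10 mg/kg over the band.
- In the other four closed rows the charted count is the best choice, with worst gaps of 2.5, 1.7, 1.8 and 2.0.
- At 11-14 kg the charted half tablet has a worst gap of 10 − 5.4 = 4.6. One tablet has 150 ÷ 11 − 10 = 3.6.
- At 36-50 kg the charted two tablets have 10 − 6.0 = 4.0. Two and a half have 10 − 375 ÷ 50 = 2.5, and three have 450 ÷ 36 − 10 = 2.5.

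So rounding does not account for the second-day count in these rows.

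**Does it explain the totals?** The same test against 25 mg/kg:
- At 11-14 kg, 2 tablets have a worst gap of 25 − 21.4 = 3.6. One and a half have 25 − 225 ÷ 14 = 8.9, and two and a half have 375 ÷ 11 − 25 = 9.1.
- At 36-50 kg, 7 tablets have 29.2 − 25 = 4.2. Six and a half have 25 − 975 ÷ 50 = 5.5, and seven and a half have 1125 ÷ 36 − 25 = 6.3.

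The charted totals are the best available in both bands. Rounding does explain them.

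**Offset from day 1.** Against 20 mg/kg over the first two days, the rows give 225 ÷ 11 = 20.5 down to 225 ÷ 14 = 16.1, and 750 ÷ 36 = 20.8 down to 750 ÷ 50 = 15.0. The two-day target is met at 11 kg and at 36-37 kg only.

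**The case against.** The strongest reply is that any chart in weight bands departs from an exact mg/kg rule, and that these two rows do well on the total. Their mean gaps from 25 mg/kg are 1.9 and 2.2, against 2.4 to 3.2 in the other closed rows. This stands. A reader might infer from the totals under 25 mg/kg at 13-14 kg and 43-50 kg (down to 21.4 and 21.0) that the chart under-doses these patients over the course. The protocol does not support that: no half-tablet total fits either band better, and similar shortfalls at 10 kg and 34-35 kg arise in the same way. Totals under 25 mg/kg above 60 kg simply follow the 1,500 mg ceiling.

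Two further replies also stand. The first-day dose is above 10 mg/kg throughout 11-14 kg and at least 10 up to 45 kg, so the second-day figure overstates the deficit at the Day 2 reading, which follows both doses. And the half-tablet comparison is a result for the band, not for each weight: at 11 kg the charted half tablet (gap 3.2) is nearer 10 than one tablet (gap 3.6). A third-day dose above 5 mg/kg is likewise not peculiar to these rows.

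Finally, the chart may reproduce the national guideline, which is not at hand. That would settle which text should govern, but the annex would still state one split and chart another. The listed syrup could deliver the stated doses, but the annex does not say who should receive it.

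**Conclusion.** The point holds for the daily split in two rows. Followed as written, the chart gives a second-day dose of 6.8 to 5.4 mg/kg at 11-14 kg and 8.3 to 6.0 mg/kg at 36-50 kg, against a stated 10, with a third-day dose of the same size against a stated 5. This assumes dispensing by whole 150 mg tablets and halves, with the row chosen by weight.

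It does not extend to the three-day totals. Nor can one infer that the failure rate would be biased or that failures in these bands reflect under-dosing: the protocol gives no weight distribution and no dose-response data, so the number of patients affected and any effect on outcome are unknown. Whether the rows are copying errors is also undetermined. It is a contradiction in a dispensing rule, worth correcting before the first patient is treated.

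**What to change.** Check both rows against the national guideline cited in the Introduction, then correct them with clinical sign-off.

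- **36-50 kg:** give the same seven tablets as 3, 2.5 and 1.5. The second day becomes 375 ÷ 36 = 10.4 to 375 ÷ 50 = 7.5 mg/kg, so the worst gap from 10 falls from 4.0 to 2.5. The third day becomes 225 ÷ 36 = 6.3 to 225 ÷ 50 = 4.5 mg/kg, so the worst gap from 5 falls from 3.3 to 1.3. The total is unchanged. A 3, 3, 1 split does no better on the second day (worst gap 2.5) and worse on the third (150 ÷ 50 = 3.0, a gap of 2.0).
- **11-14 kg:** use the listed syrup. At 50 mg per 5 ml, or 10 mg/ml, doses of 1, 1 and 0.5 ml/kg give exactly 10, 10 and 5 mg/kg. Tablets offer no good answer. Going to 1, 1 and 0.5 raises the total to as much as 375 ÷ 11 = 34.1 mg/kg. Rearranging the same two tablets either moves the low dose to day 1 (0.5, 1, 0.5) or leaves no third dose (1, 1, 0).

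If the guideline prescribes the charted rows, keep them, state that the chart governs, and describe the regimen tested to match.

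The cost is two edited rows, a syrup supply for one weight band, tablet halving in the other, and a third-day dose slightly under 5 mg/kg from 46 kg (225 ÷ 46 = 4.9). No visit or analysis is added.
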